#### 2.5.3. Exposure Variables of Interest

##### PAP Therapy and Adherence to Treatment

The gold standard treatment of moderate/severe OSA is positive airway pressure (PAP) therapy, which works by holding the airway open using a pneumatic splint. There is evidence to suggest that compliant PAP therapy use can have beneficial effects on some of the consequences of this disorder. Adherence to the treatment will be measured through an adherence tracking system using smart memory cards, which will report all needed parameters. Adherence will be primarily analyzed as a continuous variable (e.g., average hours of use per night) to capture potential dose–response relationships with cognitive outcomes. In addition, secondary analyses will examine adherence as a categorical variable using standard criteria to classify participants as adherent or non-adherent (e.g., ≥4 h of use per night [23]), allowing for clinically interpretable group comparisons. To promote participant retention and complete follow-up, study assessments are scheduled in alignment with routine clinical visits where feasible.

### 2.6. Sample Size Calculation and Power Calculations

Data collection will take place from November 2024 to September 2027 at the latest. If the targeted sample size N = 100 is reached before the end date, data collection will continue until the end of the funding.

Based on preliminary effect sizes reported in prior studies investigating PAP effects on cognition in OSA [18,19], a medium effect size (Cohen’s d = 0.5) is anticipated for within-subject changes in cognitive performance. Using G*Power 3.1.9.7, a total sample size of 34 participants is required to achieve 80% power at α = 0.05 using a two-tailed paired-samples *t*-test. This paired-samples framework provides an approximation of the within-subject effect that will be tested using linear mixed-effects models. After adjusting for an expected 15% attrition rate, this increases to 40 participants.

To support secondary analyses involving multivariable modeling, the target sample size was determined using power analyses for both the primary within-subject comparison and the planned multivariable models. The calculations assumed a medium effect size (Cohen’s f^2^ = 0.15) and up to four predictors. Accounting for an expected 15% attrition rate over the 12-month follow-up, approximately 100 participants will be recruited to ensure sufficient statistical power for all planned analyses.

The final target sample size of 100 participants was determined based on the multimodal nature of the dataset, requiring sufficient sample size for stable model estimation while limiting the number of predictors to reduce the risk of overfitting. Although the minimum required sample for detecting the expected within-subject effect is smaller, the planned sample improves the robustness of the primary outcome analysis, increases resilience to missing data, and allows for reliable adjustment for key covariates.

### 2.7. Data Analysis Plan

Descriptive statistics will be used to summarize demographic and clinical characteristics. The normality of continuous variables will be assessed using visual inspection (Q–Q plots, histograms) and statistical tests (e.g., Shapiro–Wilk). Continuous variables will be presented as mean ± SD for normally distributed data or median with interquartile range for non-normally distributed data. Categorical variables will be expressed as frequencies and percentages.

Primary analyses will evaluate within-subject changes in cognitive function over the 12-month period (i.e., change scores ΔT12–T0). These changes will be analyzed using linear mixed-effects models with a random intercept, which allow for repeated measurements and account for inter-individual variability. Fixed effects will include time, PAP adherence, and covariates such as age, sex, and education. An interaction term between time and adherence will be used to assess whether longitudinal changes differ according to adherence level.

Secondary analyses will explore associations between changes in cognitive outcomes and other measured variables, including sleep parameters, volumetric measures, anthropometric and metabolic indicators, biomarkers, and other selected laboratory measures (e.g., pNfL, ApoE genotype, gut microbiome composition), as well as indices of vascular health and autonomic nervous system function. These associations will be examined using Pearson or Spearman correlations between change scores (ΔT12–T0) and multiple linear regression models with a limited number of predictors (maximum of 4 per model) to minimize the risk of overfitting.

This study is powered to detect medium-sized effects in primary outcomes. Secondary analyses are considered exploratory and hypothesis-generating. The statistical plan will focus on core outcomes, limit the number of predictors per model, and adjust for multiple testing where applicable to minimize the risk of Type I error. Where appropriate, adjustments for multiple comparisons will be applied using procedures such as the false discovery rate (FDR) or other suitable methods. Post hoc comparisons, including subgroup analyses or alternative outcome definitions (e.g., cognitive status, biomarker levels), will be clearly identified as exploratory and interpreted with appropriate caution. Model assumptions will be assessed using standard diagnostic procedures, including evaluation of residual normality, homoscedasticity, and overall model fit. Analyses will be conducted using SPSS (version 27.0.1) or R (version 4.3.1).

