This protocol describes a prospective, observational, longitudinal cohort study. The observational design improves ecological validity by reflecting real-world patient characteristics; however, it also introduces methodological limitations that must be considered. Due to the non-randomized design and absence of a placebo or untreated control group, confounding variables cannot be fully eliminated, and causal inferences will be limited. Given the observational design, confounding by indication cannot be excluded. Although PAP therapy adherence will be objectively measured, substantial inter-individual variability in use may limit the interpretability of treatment effects. To partly address this limitation, we will perform stratified and regression-based analyses according to PAP therapy adherence levels, enabling us to explore dose–response relationships while adjusting for relevant covariates. The intentionally restrictive inclusion and exclusion criteria may raise concerns regarding both selection bias and feasibility. While these criteria were designed to reduce the influence of major confounding factors and enhance internal validity, they may result in a more selected study population and limit generalizability. However, based on preliminary analyses of patient flow at the study site, recruitment of the target sample size is considered achievable despite these constraints. The comprehensive nature of the study protocol may increase participant burden; however, the majority of assessments are part of routine clinical practice in the evaluation of patients with OSA.

In summary, this study aims to take a comprehensive approach to understanding how PAP therapy may affect cognition in OSA through an extensive assessment of various physiological and pathophysiological mechanisms. Our findings may inform future intervention strategies and improve our understanding of reversible contributors to cognitive decline.

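### Age, sex and education enter the primary mixed model without time interactions, so the time-by-adherence effect is left essentially unadjusted for them

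*Protocol article*

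**What the plan says.** Section 2.7 presents the primary analysis as one of within-person change over 12 months, identifies that change with ΔT12–T0, and continues: "These changes will be analyzed using linear mixed-effects models with a random intercept". The terms follow: "Fixed effects will include time, PAP adherence, and covariates such as age, sex, and education". One interaction is named: "An interaction term between time and adherence will be used to assess whether longitudinal changes differ according to adherence level". No covariate×time term appears anywhere in the article.

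Cognition is measured twice, at baseline and 12 months (section 2.2 and Table 1). Section 2.5.3 treats adherence mainly as a continuous variable, such as mean nightly hours, so each participant has one value. Section 2.5.1 makes adherence the exposure in the analyses of cognitive change.

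Two places describe adjustment. Section 2.6 says that the planned sample "allows for reliable adjustment for key covariates". The Discussion offers stratified and regression analyses by adherence level, "while adjusting for relevant covariates", as a partial answer to the limits of a non-randomised design. The powered target is different: in section 2.6 a medium effect "is anticipated for within-subject changes in cognitive performance", with the sample chosen "to achieve 80% power at α = 0.05 using a two-tailed" paired test.

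**The concern.** A reader who sees age, sex and education in the fixed-effects list will take the adherence result to be adjusted for them. In a two-visit random-intercept model it is not. The time×adherence coefficient compares individual changes across adherence levels, and a main-effect covariate carries no information about change.

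Participants choose how much they use PAP, and ages run from 18 to 65 (section 2.3.1). If, for example, older participants use the device more and also change differently over the year, part of that age effect would be credited to adherence. The published estimate would nevertheless carry the label of adjustment.

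The wording about change scores hides the problem. With a single change score per person as the response, main-effect covariates would adjust it. But one value per person supports neither a time effect nor a random intercept, so the listed model makes sense only for visit-level scores.

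**Working it through.** **1. The plan's own figures.** A two-sided paired t-test with d = 0.5 and α = 0.05 needs n = 34 (power 80.8%), and 34/0.85 = 40. A four-predictor regression with f² = 0.15 needs n = 85 (power 80.3%), and 85/0.85 = 100. The stated sample sizes reproduce; this point does not concern them.

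**2. Algebra.** Let t = 0 at baseline and 1 at 12 months, A = adherence, X = age, sex and education. The model as written is

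Y(i,t) = b0 + b1·t + b2·A(i) + b3·t·A(i) + g·X(i) + u(i) + e(i,t).

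The difference between visits is

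D(i) = b1 + b3·A(i) + [e(i,1) − e(i,0)].

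The terms g·X(i), u(i) and b2·A(i) drop out. The person mean over the two visits contains A only through b2 + b3/2, and b2 is free, so the mean adds nothing about b3. With complete data, the estimate of b3 is therefore the unadjusted slope of D on A, whatever main effects are listed. Adding t·X terms gives D(i) = b1 + b3·A(i) + d·X(i) + error, which is the adjusted slope.

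**3. Simulation check.** Inputs assumed, not from the documents: n = 100, SD units, true adherence effect 0, correlation of age with adherence 0.4, 300 runs per row, REML random-intercept fits.

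| Follow-up missing | Age effect on change | Mean b3, no covariates | Mean b3, main effects | Mean b3, covariate×time | Rejection rate, main effects | Rejection rate, covariate×time |
|---|---|---|---|---|---|---|
| 0 | 0 | -0.002 | -0.002 | -0.001 | 5.3% | 5.0% |
| 0 | -0.2 | -0.079 | -0.079 | 0.001 | 19.0% | 5.3% |
| 0 | -0.3 | -0.119 | -0.119 | -0.001 | 31.7% | 5.0% |
| 15% | -0.2 | -0.086 | -0.086 | -0.007 | 15% | 4% |
| 15% | -0.3 | -0.125 | -0.125 | -0.004 | 31% | 6.3% |

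With complete data, the first two models agreed in every run (maximum difference 0.0000). The bias matches the product of the inputs: 0.4 × (-0.2) = -0.08 and 0.4 × (-0.3) = -0.12. With 15% missing, main effects moved the estimate by about 0.005 to 0.006 on average and by 0.034 at most.

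**4. Size over a range of milder assumptions.** Suppose one covariate correlates r1 with adherence and r2 with change, and adherence itself has no effect. The spurious slope is r1 × r2 SD per SD. The test statistic is shifted by about |r1·r2|·√n. Take n = 85 (100 less 15%), so √85 = 9.22. The two-sided rejection rate is Φ(-1.96 + shift) + Φ(-1.96 − shift).

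| r1 / r2 | Slope | Shift | False-positive rate |
|---|---|---|---|
| 0.1 / -0.1 | -0.01 | 0.09 | about 5% |
| 0.2 / -0.2 | -0.04 | 0.37 | about 7% |
| 0.3 / -0.3 | -0.09 | 0.83 | about 13% |

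For the last row, 4,000 simulated trials gave 12.6% unadjusted and 5.4% adjusted.

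**The case against.** The strongest reply is that this is a condensed article. It does not say that covariates enter only as main effects, its covariate list is open, and an unseen analysis plan could add the missing terms. That is possible. But the open wording concerns which covariates enter, not their form, and any further baseline main effect would cancel in the same way. The article lists the fixed effects and names one interaction; fitted as described, the model gives an unadjusted adherence effect.

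A second reply is that ΔT12–T0 names the quantity of interest, not the response. That reading is reasonable, since the same section says that the model allows repeated measurements. It confirms that the response is the visit-level score, where the covariates cancel.

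Third, the adjustment sentence in the Discussion refers to regression analyses in general and would fit a regression of change on adherence plus covariates. So it would, but section 2.7 does not give that as the primary adherence analysis.

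Some stronger inferences should be resisted:
- A reader might infer that covariate adjustment is the study's only protection against confounding. It is not: the Discussion also cites restrictive eligibility and analyses stratified by adherence, and the within-person contrast removes stable differences in cognitive level. The Discussion also concedes that confounding by indication cannot be excluded. Confounding of change by these covariates is what remains.
- A reader might infer that the covariates do nothing at all. They still adjust cognitive level and the adherence main effect, and contribute slightly when follow-up is incomplete.
- A reader might infer that the whole primary analysis fails. The study is powered for average within-person change, and nothing here shows an error in that effect.

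**Conclusion.** The point holds for the time×adherence term. As specified, age, sex and education adjust it not at all with complete data and by a negligible amount with the planned 15% attrition. This is algebra for two visits, a random intercept and time-constant covariates, and does not depend on assumed effect sizes.

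The harm does depend on them. There is no bias unless a covariate relates to both adherence and 12-month change, and the documents give neither correlation. Over the range 0.1/-0.1 to 0.3/-0.3 with 85 evaluable participants, the false-positive rate runs from about 5% to about 13%. The 19% to 32% in the complete-data simulation rests on stronger assumptions and should not be read as the expected error rate.

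Severity: should be fixed. The correction is to wording and model form, and enrolment is still open (section 3), so it can be made before analysis.

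**What to change.** State in section 2.7, and in the analysis plan, that the response is the visit-level domain score at baseline and 12 months, with ΔT12–T0 as the estimand and not the response. List the fixed effects as time, adherence, time×adherence, each covariate, and each covariate×time, and apply the same rule to any baseline confounder added later. Mean-centre adherence and the covariates, so that the time coefficient remains the average change and is not the change at zero adherence and zero age.

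Regressing 12-month change on adherence plus age, sex and education gives the same adherence estimate only when both visits are complete. With 15% missing, the two differed by up to 0.066 in single simulated cohorts, so the plan should name one as primary. With education as a single term, that regression has four predictors, within the limit assumed in section 2.6.

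The cost is about three extra model degrees of freedom and some precision. In the complete-data simulation with no age effect on change, the standard error rose from 0.078 to 0.089 under the assumed 0.4 correlation. No change to design, data collection or sample size is needed.

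### With only main effects for age, sex and education, the primary mixed model leaves the time×adherence test essentially unadjusted for them

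*Protocol article*

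**What the plan says.** Section 2.7 sets the primary target: "Primary analyses will evaluate within-subject changes in cognitive function over the 12-month period (i.e., change scores ΔT12–T0". The method follows: "These changes will be analyzed using linear mixed-effects models with a random intercept". The terms are then listed: "Fixed effects will include time, PAP adherence, and covariates such as age, sex, and education". One interaction is named: "An interaction term between time and adherence will be used to assess whether longitudinal changes differ according to adherence level". No covariate-by-time term appears.

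Section 2.5.3 makes adherence a single summary per person: "Adherence will be primarily analyzed as a continuous variable (e.g., average hours of use per night". A version split at 4 h per night is secondary. Table 1 shows two cognitive assessments, at baseline and at 12 months.

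Two other places speak of adjustment. Section 2.6 says the planned sample "allows for reliable adjustment for key covariates". Section 4, on stratified and regression-based analyses by adherence level, describes them as "enabling us to explore dose–response relationships while adjusting for relevant covariates".

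**The concern.** The term of interest is a difference in change between people with different PAP use. A covariate that is constant within a person, entered only as a main effect, moves both visits by the same amount. It explains the level of cognition, not the change.

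Adherence is self-selected. If age or education is related both to PAP use and to 12-month change (for example through practice gain or ageing), that confounding stays in the time×adherence estimate. A reader who sees the covariates in the model would nevertheless take the estimate as adjusted for them.

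**Working it through.** **The plan's own figures.** These reproduce.
- Paired t-test, d = 0.5, two-sided 0.05: n = 34 (power 0.808); 34/0.85 = 40.
- Overall F test, f² = 0.15, four predictors: n = 85 (power 0.803); 85/0.85 = 100.

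So about 85 completers are expected. Neither calculation is for the time×adherence term.

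**Algebra.** For person i at visit t (0 or 1), with adherence A and covariates X, the model as written is

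y = b0 + b1·t + b2·A + b3·t·A + g·X + u + e.

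- Difference of the two visits: b1 + b3·A + (e1 − e0). The terms g·X and u are gone.
- Mean of the two visits: (b0 + b1/2) + (b2 + b3/2)·A + g·X + u + mean error. Since b0 and b2 are free, this part carries no information on b1 or b3.

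With complete pairs the two parts are independent under a random-intercept model. The estimate of b3 is therefore the ordinary regression slope of change on adherence, without X. No assumption about effect sizes is involved.

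**Numerical check.** Random-intercept models were fitted by REML to 100 simulated two-visit datasets per scenario, N = 100. Assumptions, with age and education in SD units:
- adherence = 4 + 0.8·age + 0.5·education + error (SD 1.5);
- change drifts by −0.3 per SD of age;
- visit error SD is 0.5 and intercept SD is 0.8;
- the true adherence effect on change is 0.

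Mean time×adherence estimate per hour, with the proportion of datasets giving p < 0.05:

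| Data | No covariates | Main effects only (Section 2.7) | Plus covariate×time |
|---|---|---|---|
| Complete pairs | −0.0712 (39%) | −0.0712 (39%) | 0.0002 (8%) |
| 15% random dropout | −0.0745 (35%) | −0.0742 (37%) | 0.0085 (5%) |
| 15% age-related dropout | −0.0582 (22%) | −0.0629 (27%) | 0.0040 (5%) |

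With complete pairs, the first two columns differed in any dataset by at most 5×10⁻¹⁵ in the estimate and by less than 10⁻⁶ in the SE. With dropout, the mean absolute difference was 0.003 (random) and 0.006 (age-related), and the largest was 0.019.

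In one complete dataset, both the no-covariate and main-effects models gave −0.0953 (p = 0.039), equal to the unadjusted regression of change. The covariate×time model gave −0.0152 (p = 0.75), equal to the regression of change adjusted for the three covariates.

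These inputs are strong. They imply an age–adherence correlation of 0.8/√(0.64 + 0.25 + 2.25) = 0.45 and an age–change correlation of −0.3/√(0.09 + 0.25 + 0.25) = −0.39.

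**Range of consequence.** A covariate with correlation a with adherence and b with change, and no true adherence effect, induces a spurious correlation of a·b. At 85 completers the noncentrality is about a·b·√85. For 0.3 and 0.3 that is 0.09 × 9.22 = 0.83. Simulated false-positive rates (20,000 sets, n = 85):

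| a, b | Unadjusted |
|---|---|
| 0.2, 0.2 | 6.5% |
| 0.3, 0.3 | 12.9% |
| 0.4, 0.3 | 19.6% |
| 0.4, 0.4 | 30.8% |

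After adjusting change for the covariate, the rates were 4.6% to 5.3%.

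**The case against.** **The article does not say the covariates enter only as main effects.** True: the covariate list is illustrative, and a fuller plan could add interactions. But the article lists the fixed effects and then names one interaction. Its plain reading is a model that does not adjust this term, so the issue is what is specified and not a missing detail.

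**Section 2.7 calls the outcome a change score, and then main effects would adjust.** That is correct for a regression of change. But with one change score per person, the time term, the time×adherence term and the random intercept have no role. The wording shows that the passage needs reconciling; it does not rescue the model described.

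**A reader might infer that the article claims an adjusted adherence effect from the primary model.** The text does not go that far. The sentence in Section 2.6 does not mention adherence, and the one in Section 4 does not name the mixed model. The secondary change-score regressions, with up to four predictors, could adjust.

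**A reader might also infer that no adjustment of any kind takes place.** That is too absolute. The exact identity needs complete pairs; with dropout the covariates have a small effect on the term. They also adjust the level of cognition and the adherence main effect.

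**Confounding is already conceded.** Section 4 says it cannot be fully eliminated and that confounding by indication cannot be excluded. This stands and lowers the severity. It does not explain why covariates named in the primary model should do almost nothing for its adherence test.

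**Conclusion.** The point holds for the model as written. The primary test of whether change differs by adherence is unadjusted for age, sex and education with complete pairs, and nearly so at 15% attrition. The complete-pairs result is algebra.

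The size of any bias is not established. The article gives no correlation of these covariates with PAP use or with 12-month change. The false-positive rates of 6.5% to 30.8% rest wholly on assumed correlations, and the lower end is close to nominal. The documents do not support a statement that the adherence result will be confounded by a given amount.

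This should be fixed but is not critical: residual confounding is acknowledged, and the paired power calculation concerns the overall within-subject change, not the adherence slope.

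**What to change.** In Section 2.7, add age×time, sex×time and education×time to the fixed effects of the primary mixed model. Do the same in the secondary version with adherence as at least 4 h versus less.

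In the same section, state whether the outcome is the repeated score or the change. If it is the repeated score, drop the change-score description of the model. If it is the change, regress 12-month change on adherence plus the three covariates, and remove the time term, its interaction and the random intercept. That regression matches the extended mixed model only for complete pairs, and it cannot use participants with a baseline score alone, whose data Section 2.8 keeps in the analysis. A regression of the 12-month score adjusted for baseline targets a different estimand and should not be treated as interchangeable.

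The cost is a short edit and three degrees of freedom if education is a single term: for change at 85 completers, residual degrees of freedom go from 85 − 2 = 83 to 85 − 5 = 80. No new data are needed, and enrolment was still ongoing when the article was submitted.

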### 2.1. Study Aims and Hypotheses

The primary aim of this study is to perform a detailed cognitive assessment in patients with OSA. We aim to analyze the baseline prevalence, severity, and pattern of cognitive deficits in this population and to evaluate changes in cognitive function after 12 months of PAP therapy to gain a clearer understanding of the initial cognitive status from which potential therapeutic or disease-related changes may occur.

The secondary aims of this study are exploratory. We plan to investigate associations between cognitive outcomes and a broad spectrum of OSA-related measures, including polysomnography (PSG)-derived sleep parameters, brain volumetric measures, anthropometric and metabolic indicators, biomarkers (e.g., pNfL, oxidative stress markers, lipid subfractions, ApoE genotype), gut microbiome composition, vascular function, and autonomic nervous system regulation. We also aim to explore how PAP adherence relates to longitudinal changes in these cognitive and physiological outcomes.

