## 4. Discussion

As the population ages, more adults experience stroke, cognitive impairment, and dementia. Because no effective treatments currently exist to prevent or slow dementia, identifying modifiable risk factors such as OSA is increasingly important [24].

OSA has been linked to substantial cognitive, metabolic, and cardiovascular consequences [3,4,5,6], yet the extent to which these impairments are reversible with long-term therapy remains unclear. By combining a neuropsychological assessment, physiological measures, neuroimaging, and biomarkers, this study provides a systems-level approach to understanding the pathophysiological mechanisms of untreated OSA and the therapeutic potential of PAP therapy.

Previous meta-analytic findings suggest that cognitive impairment in OSA is domain-specific, with the most consistent deficits observed in executive functions, attention, and information processing speed, while other domains such as memory may be less consistently affected. However, the relationship between OSA severity and cognitive outcomes appears heterogeneous and not strictly linear. Methodologically, many existing studies have relied on brief cognitive screening tools and relatively short durations of PAP therapy, which may limit the detection of subtle or domain-specific changes [4]. Complex neuropsychological assessment both before and after intervention may provide stronger empirical support for the connection between OSA and cognitive impairment or reveal new associations. Through PAP treatment, we aim to investigate whether its use is linked to functional brain changes. To our knowledge, no previous study has investigated these relationships with such an extensive multi-modal assessment and controlled set of underlying pathophysiological mechanisms.

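### The secondary change-score correlations take no account of PAP adherence, and no section commits the accompanying regressions to include it, so a shared PAP effect can make two otherwise unrelated changes correlate

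*Protocol article*

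**What the plan says.** Section 2.7 gives two tools for the secondary associations. The first is bivariate: the associations "will be examined using Pearson or Spearman correlations between change scores". The second, in the same sentence, is "multiple linear regression models with a limited number of predictors (maximum of 4 per model) to minimize the risk of overfitting". The predictors are not named.

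Adherence is placed in a model explicitly only for the primary analysis: "Fixed effects will include time, PAP adherence, and covariates such as age, sex, and education", with a time-by-adherence interaction. It also appears elsewhere in the plan:

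- Section 2.1 states the aim to "explore how PAP adherence relates to longitudinal changes in these cognitive and physiological outcomes".
- Section 2.5.3 makes adherence the exposure of interest, mainly as continuous hours of use, with a categorical version in secondary analyses.
- The Discussion says "we will perform stratified and regression-based analyses according to PAP therapy adherence levels", with covariate adjustment.

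None of these says that the associations between cognitive change and physiological change will be adjusted for adherence.

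**The concern.** Three features of the plan combine.

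- **PAP exposure differs between participants.** Under Section 2.2 only those with a routine clinical indication are treated, Table 1 records adherence only where it applies, Section 2.8 keeps participants who discontinue, and the Discussion expects wide variation in use.
- **The protocol allows PAP to act on both sides.** Sections 2.1 and 2.5.2 look for a relation of PAP with cognitive change and with change in the other measures.
- **The first-named secondary tool has no place for a third variable.**

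If adherence moves both change scores, they correlate even when neither has anything to do with the other. Any measure that responds to PAP then tends to correlate with any cognitive domain that responds to PAP, and the screen cannot tell a candidate mechanism from a bystander. The false discovery rate procedure in Section 2.7 limits chance findings. An induced correlation is a real non-zero correlation, so the procedure treats it as a true discovery.

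This matters because the Discussion says "this study provides a systems-level approach to understanding the pathophysiological mechanisms of untreated OSA and the therapeutic potential of PAP therapy". Raw change-change correlations alone would not carry a statement of that kind.

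**Working it through.** **Number of completers.** Section 2.6 gives f² = 0.15, up to four predictors, 15% attrition and about 100 recruited. Taking α = 0.05 and 80% power from the paired calculation in the same section, the overall F-test with four predictors needs N = 85 (power 0.803), and 85 / 0.85 = 100. The plan's figure reproduces, so n = 85 is used below.

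**Assumptions, not in the documents.** Let A be adherence, X the physiological change and Y the cognitive change. A correlates a with X and b with Y, and X and Y have no other connection. Values of 0.2 to 0.6 are tried because the protocol gives none.

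**Formulas.**

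- Induced correlation: r = a × b.
- Probability that the raw correlation is significant (Fisher z): m = atanh(r) × √(n − 3), and P = 1 − Φ(1.96 − m) + Φ(−1.96 − m).
- Partial correlation: (r_XY − r_AX × r_AY) / √[(1 − r_AX²)(1 − r_AY²)].

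**Worked case, a = b = 0.4.** r = 0.16; atanh(0.16) = 0.1614; √82 = 9.055; m = 1.461; P = 0.31. The numerator of the partial correlation is 0.16 − 0.4 × 0.4 = 0, so the adjusted test rejects at its nominal 5%.

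| a, b | Induced r | Raw test significant at 0.05 | Given adherence |
|---|---|---|---|
| 0.2, 0.2 | 0.04 | about 7% | about 5% |
| 0.2, 0.3 | 0.06 | 8.5% | about 5% |
| 0.3, 0.3 | 0.09 | 13% | about 5% |
| 0.4, 0.4 | 0.16 | 31% | about 5% |
| 0.3, 0.5 | 0.15 | 28% | about 5% |
| 0.5, 0.5 | 0.25 | 64% | about 5% |
| 0.5, 0.6 | 0.30 | 80% | about 5% |

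Simulation at n = 85 with 20,000 or more runs per row agrees with the formula to within about one percentage point.

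**Power cost of adjusting.** Suppose X has a real standardised coefficient of 0.3 on Y, A correlates 0.4 with X, and A has no direct effect on Y. Then r_XY = 0.30 and r_AY = 0.4 × 0.3 = 0.12.

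- Raw: atanh(0.30) × √82 = 0.3095 × 9.055 = 2.80, power about 80%.
- Adjusted: partial r = (0.30 − 0.048) / √(0.84 × 0.9856) = 0.277; atanh(0.277) × √81 = 0.2844 × 9 = 2.56, power about 73%.

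The loss is about 7 points. Adherence fits within the four predictors already allowed for, so the 85 completers and 100 recruits stand.

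**The case against.** The strongest reply is that the plan does not leave adherence out of the secondary work. The sentence on correlations goes on to multiple regression, whose predictors could include adherence, and the Discussion plans stratified and regression-based analyses by adherence level. Choosing covariates for exploratory models is often left to a fuller plan. This stands: a reader might infer that the secondary analyses exclude adherence altogether, and the document does not say so. The unnamed predictors are not an error in themselves. What remains is that the correlations, which are fixed in the text, are unadjusted, and that the adherence-level analyses are described as dose-response work without being tied to the cognition-physiology associations.

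A reader might also infer that a shared PAP effect will be reported as a mechanism. The documents do not support that either. Sections 2.5.2 and 2.7 label the secondary analyses exploratory, the Discussion says causal inference will be limited, and a raw correlation is a valid answer to which changes occur together. The mechanism wording is general Discussion text.

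The size is assumed throughout. At 0.2 on each side the distortion is slight, and the 64% figure requires adherence to explain 25% of the variance of both changes (0.5²). The rates are per test at an uncorrected 0.05. The return to 5% holds because adherence is the only shared cause in the calculation and is measured without error.

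Adjustment has limits of its own. Adherence builds up over the same 12 months as the changes and may partly respond to them. For polysomnographic measures, which PAP alters directly, adjustment may remove much of the variation of interest. These are good reasons to show both results and not to replace the raw correlation.

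**Conclusion.** The point holds in a limited form. The stated bivariate correlations cannot separate a direct link between a physiological and a cognitive change from a PAP effect common to both, and the protocol does not commit the accompanying regressions to do so. Under the assumed range of 0.2 to 0.5 on each side with 85 completers, two unrelated changes would correlate significantly in about 7% to 64% of cases instead of 5%. This rests on adherence truly affecting both changes, which the study sets out to examine and the documents do not quantify. The primary mixed model, which includes adherence and its interaction with time, is not affected.

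**What to change.** In Section 2.7:

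1. Beside each raw change-change correlation, report the partial correlation given continuous PAP adherence (average hours per night).
2. Reserve one of the up to four predictors in the change-score regressions for adherence.
3. State how participants not prescribed PAP are coded so that they are not dropped, for example zero hours, with a sensitivity analysis among PAP users only.
4. Describe raw correlations as associations only, and base any statement about candidate mechanisms on the adjusted result. Note that other shared causes, such as weight change, remain.

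Adherence is already being collected and enrolment is ongoing, so this is a change of wording made before analysis. The price is one predictor slot and the power loss shown above; the target of 100 does not change.
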